### Outcomes

#### Efficacy

The primary outcome will be the proportion of participants testing positive at least once for up to three independent assays of polymerase chain reaction (PCR) during the 12–18 months after the initiation of treatment, with an interval of 7 or more days from each other. Secondary efficacy outcomes will be (1) the mean change in the levels of B-type natriuretic peptides (either NT pro-BNP or BNP, as long as the same test is used for each participant) and (2) the proportion of participants with positive serological status (using conventional serology diagnosis) 12 months after the initiation of treatment. Centres outside Colombia may or may not, depending on the resources available and practice patterns, provide data on BNP or conventional serology after treatment. All efficacy outcomes will be recorded and analysed without knowledge of treatment allocation.

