### Study procedures and follow-up of participants

Once they have been screened for eligibility, offered participation in the study and have given their consent, candidates will start the run-in phase (visit 0). Study physicians will rule out any exclusion criteria for those completing this phase and, for those still eligible, will randomise a new participant (visit 1). The participants will receive the allocated treatment for the first 60 days and will be asked to attend a number of follow-up visits during treatment. These visits allow reporting of any potential side effects as well as providing physical exams and/or blood work safety monitoring. For Colombian centres, the visits are scheduled at days 20, 30 and 60, repeating the cycle when a second 60-day cycle starts.

In the presence of signs of intolerance, study physicians may decide to stop the study medication temporarily or definitely. They may also prescribe a symptomatic treatment (e.g. an anti-histaminic for pruritus) to participants over the study period or refer to treating physicians or medical emergency services when they judge it may be necessary. Adherence, as the reciprocal proportion of scheduled treatment that participants left unused, will be assessed at visits 2 through 7. Efficacy outcome data will be collected during months 12 to 18 after treatment start, scheduling three separate visits (with at least 1 week of separation) at each participant’s convenience. Table 2 summarises the study follow-up visits scheme. The Standard Protocol Items: Recommendations for Interventional Trials (SPIRIT) checklist is included as an additional file (see Additional file 1).

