**Table 2 Tab2:**
[figure not shown]
Overview of study visits and procedures

The visit schedule may vary at centres outside Colombia, according to the chosen study groups, the practice patterns and preferences. In all cases, however, the schedule should include in-person evaluations (also allowing for blood safety monitoring) at least every 30 days (i.e. 30, 60, 90 for those testing 120-day treatments), at end of treatment and 1 year after randomisation (for outcome assessment). Visit scheduling will adjust for centres testing only 60-day treatments. For those having 120HD treatments, it will be necessary to renovate the study treatment at 60 days in order to re-supply participants with the rest of the intervention and to test adherence. When applicable, these centres will decide whether or not to include a new follow-up visit to promote adherence for the next period and/or test safety (if so, including blood work). All centres must also commit to schedule additional visits at any other time during treatment upon a participant’s request.

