### Sample size calculations

The planned hypotheses in this study will be based on the following assumptions for its sample size:The proportion of participants in the placebo group with at least one positive PCR out of three tests (1 + PCR, the primary outcome for efficacy) will be 75% or higher.As a standard of trypanocidal efficacy, the proportion of (1 + PCR) in the group receiving conventional treatment with BZN (based on results of the BENEFIT trial) will be up to 30% (or 25% in a group receiving BZN in a regime with better tolerance).A treatment with NFX, to be considered non-inferior to BZN, should have at least two thirds of its trypanocidal effect, which is, in terms of the above assumptions, 45% of 1 + PCR (or up to 50% in a group receiving a regime with lower tolerance/efficacy).

Based on the above assumptions, having at least 60–80 participants per study group will allow enough (at least 80%) power to identify a true difference between NFX and placebo or BZN (as negative or positive control for superiority or non-inferiority, respectively), testing a one-tailed hypothesis at an alpha level of 1%. Colombian centres should account for at least 60% of the study population, or 300 participants in the study (60 participants for each group). The overall goal of recruitment, including participants for centres outside Colombia, will be 500, as long as they include at least 80 participants allocated to every study arm (which may vary, depending on the treatment groups chosen at centres outside Colombia). Table 3 shows the scenarios for power calculations for the comparisons on efficacy.

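### The primary outcome allows one, two or three PCRs while the sample size assumes three, so uneven testing would dilute differences and ease non-inferiority

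*Protocol article*

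**What the plan says.** Four places in the protocol article bear on how many PCRs stand behind the primary outcome.

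- **Outcomes, Efficacy:** the outcome is "the proportion of participants testing positive at least once for up to three independent assays of polymerase chain reaction (PCR", in months 12–18, with assays at least 7 days apart. A maximum is given and no minimum. The Abstract uses the same up-to-three form.
- **Sample size calculations:** the placebo rate is for participants "with at least one positive PCR out of three tests (1 + PCR, the primary outcome for efficacy) will be 75% or higher". The benznidazole (BZN) rate "will be up to 30% (or 25% in a group receiving BZN in a regime with better tolerance", and the nifurtimox (NFX) limit is "45% of 1 + PCR (or up to 50% in a group receiving a regime with lower tolerance/efficacy". All are on the same 1 + PCR measure.
- **Study procedures and follow-up:** efficacy data come from "scheduling three separate visits (with at least 1 week of separation".
- **Same section, text after Table 2:** the schedule may vary outside Colombia. The required in-person evaluations are those during treatment, then "at end of treatment and 1 year after randomisation (for outcome assessment".

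Colombia is to supply at least 60% of participants (300 of 500), so other centres supply at most 40%.

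**The concern.** The chance of at least one positive result rises with the number of tests. An outcome that accepts one, two or three tests therefore measures something different in participants tested a different number of times. Because assays must be at least 7 days apart, a single outcome visit yields one qualifying assay.

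If some participants have fewer tests and the definition is applied as written, more of them are classed as negative in every arm, and absolute differences between arms shrink. For NFX against placebo this costs power. For NFX against BZN, and for 60CD against 120HD, it brings the arms closer together while an absolute margin stays where it was, so a regimen at the limit of acceptability is more likely to be declared non-inferior. At an alpha of 1%, a modest shrinkage is visible.

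**Working it through.** **Inputs from the article.** Three-test rates: placebo 75%, BZN 30% (or 25%), NFX limit 45% (or 50%). One-sided alpha 1% (z = 2.326). 60–80 per group, 5% losses. Non-Colombian share at most 200/500 = 40%.

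**Assumption.** The article does not give the correlation ρ between a participant's repeat PCRs. I use a beta-binomial model with ρ of 0, 0.4, 0.6 and 0.8.

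**Step 1: the plan's own figure.** With one-sided 1%, 80% power and three-test rates, 75% v 50% needs 74 per group (74/0.95 ≈ 78 with losses) and 75% v 45% needs 53 (56). Non-inferiority with a 25-point margin needs 61 (65) at 25% v 25% and 68 (72) at 30% v 30%. These support the stated 60–80, so that range matches rates defined on three tests. The cells of Table 3 are not shown and were not checked.

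**Step 2: single-test rates.** For ρ = 0, q = 1 − (1 − P₃)^(1/3). For example, 1 − 0.25^(1/3) = 0.370. For ρ > 0, solve 1 − P₃ = ∏ (b + i)/(s + i) over i = 0, 1, 2, with s = (1 − ρ)/ρ and b = s(1 − q).

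| Three-test rate | One test, ρ = 0 | ρ = 0.4 | ρ = 0.6 | ρ = 0.8 |
|---|---|---|---|---|
| 75% | 37.0% | 52.7% | 61.0% | 68.6% |
| 50% | 20.6% | 30.0% | 35.9% | 42.6% |
| 45% | 18.1% | 26.4% | 31.6% | 37.9% |
| 30% | 11.2% | 16.4% | 19.9% | 24.4% |

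**Step 3: upper-bound mixture.** If every non-Colombian participant had exactly one test, the observed rate is 0.6 × P₃ + 0.4 × q. At ρ = 0:

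- 75% becomes 59.8%
- 50% becomes 38.3%
- 45% becomes 34.2%
- 30% becomes 22.5%

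**Step 4: non-inferiority error at the limit.** Each compared group pools two arms: 2 × 80 × 0.95 = 152. Error = Φ[(0.15 − d)/SE − 2.326], where d is the diluted 45% v 30% difference. At ρ = 0, d = 0.117 and SE = 0.0513, so (0.15 − 0.117)/0.0513 ≈ 0.635 and Φ(0.635 − 2.326) ≈ 4.5%.

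**Step 5: superiority power, 75% v 50%, 80 per group.** Pooled variance under the null, unpooled under the alternative.

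- Three tests: (0.25 − 2.326 × 0.0766)/0.0740 = 0.97, power 83.5%.
- Mixture at ρ = 0: (0.2155 − 2.326 × 0.0790)/0.0772 = 0.41, power 66%.

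| 40% with one test | ρ = 0 | 0.4 | 0.6 | 0.8 |
|---|---|---|---|---|
| 15-point gap becomes | 11.7 | 13.0 | 13.7 | 14.4 |
| Error, 15-point margin, 152 per group | 4.5% | 2.6% | 1.9% | 1.3% |
| Error, 25-point margin (25% v 50%), 80 per group | 6.1% | 3.2% | 2.1% | 1.4% |
| Power, 75% v 50%, 80 per group | 66% | 77% | 82% | 84% |

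The primary superiority comparison pools both NFX arms. At 160 v 80 with three tests the power is 93%. With the ρ = 0 mixture it is Φ[(0.2155 − 2.326 × 0.0682)/0.0669] ≈ 80%.

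**Step 6: margin read as effect retention.** The criterion is that NFX keeps two thirds of the BZN effect, so test θ = p_NFX − (2/3)p_BZN − (1/3)p_placebo, which is 0.45 − 0.20 − 0.25 = 0 on three tests. With the same mixture and 76 on placebo (80 × 0.95), θ shifts by less than 0.01 and the error is 1.3–1.6% over ρ from 0 to 0.8.

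**The case against.** Several stronger readings are tempting, and the article does not support them.

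- **That outside centres will do one PCR.** The three-visit sentence is not restricted to Colombia; only the on-treatment visit days are. The outcome section lets outside centres omit natriuretic peptide and serology data and does not list PCR. Table 2 is not shown. One visit is a permitted minimum and not a stated plan.
- **That missing tests are scored as negative.** No sentence says so. It is the literal result of an up-to-three definition with no minimum, and an unseen analysis plan may handle it otherwise.
- **That the error could be far higher if everyone had one test.** That conflicts with the three scheduled visits and with Colombia's share of at least 60%.
- **That one arm is favoured.** Comparisons are between groups randomised at the same centre, randomisation is stratified by centre, and efficacy assays are run centrally and blinded after follow-up ends. The centre schedule therefore applies equally to all arms. Bias in one direction needs completed test counts to differ by arm. Open-label centres make that possible, but nothing in the article shows it.

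Two points on size also stand. A high correlation between repeat tests makes the effect small, and a retention criterion absorbs most of the inflation. The planned analysis of Colombian participants alone would help expose a centre effect, but it does not cover tests missed within Colombia.

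What this leaves untouched is that the outcome definition, the sizing assumption and the minimum visit schedule do not agree. That is a matter of stated text and not of detail left to an analysis plan.

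**Conclusion.** The point holds in limited form. The outcome definition sets no minimum number of tests, the sample size is built on "at least one positive PCR out of three tests", and the follow-up text can be read as either three outcome visits or one outside Colombia. Applied literally, this dilutes differences, which lowers superiority power and eases a non-inferiority claim against an absolute margin.

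The size is uncertain. At the upper bound of 40% single-test, the nominal 1% error at a 15-point margin lies between about 1.3% and 4.5%. Power for 75% v 50% at 80 per group lies between about 66% and 84%, against 83.5%. Both ranges rest on an assumed correlation of 0.8 down to 0. The true effect is smaller if outside centres do three tests, if their share is below 40%, or if the margin is applied as effect retention.

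**What to change.** Reconcile the outcome definition, the three-visit schedule, the minimum schedule outside Colombia and the sample-size assumption, so that the outcome is defined on three PCRs at all centres. Then state the scoring:

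- Any positive PCR is an event, whatever the number of tests.
- No positive with fewer than three valid PCRs is incomplete, not negative.
- Incomplete outcomes are handled by multiple imputation of the missing tests (by arm, centre and results so far), or by a per-test model such as beta-binomial or GEE logistic from which the three-test rate is derived.
- The crude up-to-three rule is kept as a sensitivity analysis.
- The number of completed PCRs is reported by arm and centre.

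Efficacy samples are processed together after follow-up ends, so the rule can be fixed before any result is known. The cost is modest extra analysis and slightly wider intervals.

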### Setting and participants

EQUITY will seek collaborating centres from Colombia and other countries in Latin America offering care to outpatients with *T. cruzi* chronic infection. Study centres will be actively seeking eligible candidates with local centres for serology diagnosis, blood banks or health authorities. The eligible population will be individuals aged 20–65 of both sexes, with serology diagnosis (positive results for at least two out of three serological tests including enzyme-linked immunosorbent assay [ELISA] and indirect immunofluorescence of haemagglutination over the last 10 years), negligible risk of re-infection (residence in an urban setting or a suburban/rural area with no history of vector infestation or transmission) and the capability to attend regular follow-up visits at the study centres (Table 1).

**Table 1 Tab1:** Study eligibility criteria

Eligibility	Exclusion criteria
• Men or women 20–65 years of age	• Previous treatment with nifurtimox or benznidazole
• Positive serology for *T. cruzi* (at least two different techniques applied to the same blood sample) in the last 10 years	• Lack of compliance/tolerance to a 10-day run-in period
• No clinical suspicion, or active risk factors for, chronic cardiomyopathy	• Abnormal values in blood cell counts or laboratory tests for hepatic and renal function
• Negligible risk of vector *T. cruzi* re-infection	• Any medical/social condition hindering free participation
• Capable of complying with the planned study visits	• Current or planned pregnancy, or not using secure birth methods for women of childbearing age

Exclusion criteria include the following: previous treatment with BZN or NFX or participation in trials testing trypanocidal drug candidates; any symptom suggesting chronic Chagas (or other forms) of cardiomyopathy or uncontrolled risk factors for it; persistent abnormalities in liver/kidney blood function tests (alanine amino transferase [ALAT]/aspartate amino transferase [ASAT] twofold normal values or creatinine over 1.2 mg/dl observed at least twice); women of childbearing age who have positive pregnancy tests or are unwilling to use secure birth control methods; or any concomitant health problem judged by the study physician as potentially interfering with free participation, health or well-being during the study or administration of treatment.

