### Laboratory testing

As presented in Table 2, some of the visits will include laboratory testing for treatment safety monitoring or study outcomes. The former includes blood cell counts and liver and kidney function tests, and the latter conventional *T. cruzi* serology and brain natriuretic peptides. Processing of blood safety monitoring tests will take place at referral laboratories for each centre as every participant attends his/her follow-up visits. Efficacy outcome data will have, in contrast, a centralised collective processing on stored samples in laboratories of reference once the follow-up of participants has finished. Participants will be individually informed of the results of these tests (the safety monitoring during the follow-up visits and the efficacy outcome when they are processed) and be given individualised copies of the laboratory reports.

Processing and interpretation for *T. cruzi* serology and BNP assays will follow recommendations of the makers of approved, commercially available assays. Techniques for PCR will follow consensus recommendations described elsewhere [16, 17]. Collection requires at least 3.5 mL of whole blood in tubes with ethylenediaminetetraacetic acid (EDTA), in triplicate. These samples are then mixed into equal parts with guanidine hydrochloride-6 M EDTA and stored at 4 °C (2–8 °C) until processing. Aliquots of 500 μL will be taken to conduct the extraction of DNA using the High Pure PCR Template Preparation Kit (Roche). Analysis of DNA samples using real-time PCR amplifies the repetitive region of DNA of the parasite with the initiators cruzi1 and cruzi2. For conventional PCR we will use the primers S21 and S22. The lab will conduct triplicate analyses of the blood samples, and the absolute quantification of the parasite will be the average of the replicates.

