### Statistical analysis

Reporting of trial results will include a description of the enrolment process and the most relevant characteristics of the participants. For this purpose we will use counts and proportions or means and standard deviations for discrete and continuous variables, respectively.

Our outcome measures will be discrete variables, with the exemption of mean changes in the BNP levels, a secondary outcome for efficacy. For the purpose of evaluating the efficacy of NFX over placebo, we will test a hypothesis of no difference in the proportions of 1 + PCR at an alpha level of 1%. For the purpose of testing the equivalence of NFX to BZN or between 60CD and 120HD regimes, we will run a one-tailed non-inferiority test at an alpha level of 1%. In order to test for agent-dose interaction for the above comparisons, we will construct logistic regression models with the primary outcome as the event, and the comparison groups and study arms (e.g. NFX 60CD or NFX 120HD) as predictor variables. We will include the interaction dose*agent term in the model and run this test for no differences at an alpha level of 5%.

For the purpose of evaluating mean changes of BNP among groups, we will test for differences using independent-sample Student’s *t* tests comparing the groups of interest (alpha level of 1%). For the dose-agent interaction test (alpha level 5%), we will run an analysis of covariance with the mean changes as response, the comparison and study arms as factors and the interaction term.

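### Secondary serology outcome is analysed only as positive or negative at 12 months in participants enrolled as seropositive, so an antibody fall that stays above the cut-off counts as no change; the power loss can be large but is conditional

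*Protocol article*

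**What the plan says.** Under Outcomes, Efficacy, the second secondary outcome is "the proportion of participants with positive serological status (using conventional serology diagnosis) 12 months after the initiation of treatment". The Statistical analysis section fixes its scale: "Our outcome measures will be discrete variables, with the exemption of mean changes in the BNP levels, a secondary outcome for efficacy". So the plan contains no analysis of antibody level.

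Eligibility depends on the same kind of test. Setting and participants asks for "positive results for at least two out of three serological tests including enzyme-linked immunosorbent assay" or the other listed techniques, and Table 1 words the criterion as "at least two different techniques applied to the same blood sample) in the last 10 years".

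Two further statements bear on the point. Laboratory testing says "Efficacy outcome data will have, in contrast, a centralised collective processing on stored samples in laboratories of reference", and that serology is processed and interpreted as the assay makers recommend. The Efficacy section adds: "Centres outside Colombia may or may not, depending on the resources available and practice patterns, provide data on BNP or conventional serology after treatment".

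**The concern.** Everyone is enrolled on the positive side of a threshold, and the outcome asks only who is on the other side a year later. Participants well above the cut-off can lose a good deal of antibody and still be scored as unchanged. If most stay above it, the arms will all sit near 100% positive whatever the drugs have done, and the comparison will have little power.

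Serology is the only efficacy outcome besides PCR that bears on the parasite, so a flat result invites comment in a trial about superiority over placebo and non-inferiority to BZN. The other secondary marker, BNP, is analysed as a mean change, and the article gives no reason for treating the two differently. Because the article states the scale, this is a choice made in the text and not a detail left to an unseen SAP.

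**Working it through.** **The plan's own figure.** The sample size rests on PCR alone, at 1% one-sided. For 75% against 50% positive, placebo against the two NFX groups at 1:2 and 80% power, the two-proportion formula gives 57 placebo participants, and 57/0.95 = 60 with 5% losses. At 90% power it gives 72, or 76 with losses. The stated 60–80 per group is reproduced. No figure is stated for serology.

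**Inputs.**
- Colombia, 60 per group less 5% (Sample size calculations; Table 3 footnote): placebo 60 × 0.95 = 57; pooled NFX 2 × 57 = 114.
- Alpha: one-sided 1%, carried over from the sample size section. The article sets no alpha for serology, so this is an assumption.
- Responder share f, borrowed from the article's PCR rates: (75 − 50)/75 = 1/3 and (75 − 25)/75 = 2/3. The 25% is the article's figure for a better-tolerated BZN regime; its NFX figures are 45–50%, given as a non-inferiority bound. Applying f to antibody response is an assumption.
- Share c of controls negative at 12 months: 1%, 2% or 5% (assumed).
- Fall D in responders: 1, 1.5, 2 or 3 SD of the log level (assumed).

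**Formulas.**
- Negative share on NFX: q = (1 − f)c + f·Φ(Φ⁻¹(c) + D).
- Binary power: exact enumeration of Binomial(114, q) and Binomial(57, c), rejecting when the pooled z statistic reaches 2.326.
- Continuous power: Φ(fD/SE − 2.326), with SE² = [1 + f(1 − f)D²]/114 + 1/57.

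**Worked cell** (D = 1, f = 2/3, c = 2%). Φ⁻¹(0.02) + 1 = −1.054 and Φ(−1.054) = 0.146, so q = 0.02/3 + 0.146 × 2/3 = 0.104. Binary power for 10.4% against 2% negative is 29%. For the level, SE = √(1.222/114 + 1/57) = 0.168, and Φ(0.667/0.168 − 2.326) = Φ(1.64) = 95%.

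**Grid.**

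| Fall | Responders | Binary power, c = 1% / 2% / 5% | Continuous power |
|---|---|---|---|
| 1 SD | 1/3 | 0.2% / 3% / 15% | 37% |
| 1 SD | 2/3 | 7% / 29% / 61% | 95% |
| 1.5 SD | 1/3 | 14% / 34% / 55% | 70% |
| 1.5 SD | 2/3 | 77% / 93% / 98% | 100% |
| 2 SD | 1/3 | 70% / 83% / 88% | 90% |
| 2 SD | 2/3 | about 100% throughout | 100% |
| 3 SD | either | at least 99% | at least 99% |

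Binary power is below half the continuous power in 7 of the 24 cells: all three in row 1, the first two in row 2 and the first two in row 3.

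**Cross-check with a different model.** Take a uniform shift of 0.6 SD, two-sided 1%, 60 against 120. The continuous level has 89% power. The binary outcome has about 4%, 9% and 23% when 99%, 98% and 95% of placebo participants stay positive. The asymptotic efficiency of the cut, φ(z)²/[p(1 − p)] with p the share positive and z the matching normal quantile, is 7% at 99% positive and 22% at 95%.

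**Where the loss disappears.** With no seroreversion on placebo (exact test, two-sided 1%, 60 against 120), binary power is 2%, 25%, 54% and 96% if 5%, 8%, 10% and 15% of NFX participants serorevert.

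**The case against.** The strongest reply is that the effect sizes are all assumed. The documents do not say how far antibody falls by 12 months, how many participants serorevert, or that a PCR response implies an antibody response. This stands. The grid shows what could happen, and most of its cells do not lose half the power. In the row with a 1 SD fall and one third responding, the continuous analysis reaches only 37%, so it would not rescue the comparison there.

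Several stronger readings are tempting and are not supported:
- *Most power is lost.* That holds only when falls are modest and nearly everyone stays positive.
- *The outcome starts at exactly 100%.* Entry serology may be up to 10 years old, and the text reports no baseline repeat (Table 2 is not shown).
- *A numeric readout from a single batch already exists.* The article says collective processing in reference laboratories, in the plural. It names no assay for the outcome and mentions no quantitative export.
- *A flat result would count as support for equivalence.* The plan specifies no non-inferiority test for serology. The risk lies in interpretation and is not written into the plan.

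The model also uses one cut-off on one index, whereas diagnosis at entry combines techniques. Finally, the proportion still seropositive is directly interpretable, and a fall in index is less readily read as cure. That is a good reason to keep the proportion, but not to make it the only analysis.

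**Conclusion.** The point holds as a limitation of one secondary outcome. The stated scale discards any antibody fall that stays above the cut-off. The cost ranges from none (3 SD fall, or 2 SD with two thirds responding) to very large (1 SD fall with two thirds responding: 7–61% power against 95%). Where the trial will fall in that range cannot be settled from the documents. The figures rest on a normal log antibody level, a one-sided 1% test, 1–5% of controls negative, and responder shares borrowed from PCR. Serology is optional outside Colombia, so the number analysed may not grow much beyond 60 per group.

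A reader might infer that the trial's efficacy conclusions are at risk. They are not: the primary PCR comparisons and the sample size do not depend on serology.

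**What to change.** In the Efficacy and Statistical analysis sections, add the log ELISA index (or log2 titre, where the assay used gives a numeric readout) at the 12-month outcome visit as a continuous secondary analysis. Use the same assay for all participants and compare arms with a linear model. Include the baseline value as a covariate where a stored baseline sample exists. List this outcome with BNP as an exception to the discrete outcomes.

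Keep the proportion still seropositive as a reported outcome beside it. State that similar proportions near 100% in all arms are not evidence of equivalence or of no effect.

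The cost is an amendment, made before the outcome samples are unblinded, plus numeric results from the reference laboratories where the assay provides them. No extra participants or visits are needed. The small downside is the less direct reading of an index fall, which reporting the proportion offsets.
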